## Abstract

Diet quality influences glycemic control in people with type 2 diabetes (T2D), impacting their risk of complications. While there are many cross-sectional studies of diet and diabetes, there is little understanding of the extent to which people with T2D change their diet after diagnosis and of the factors that impact those changes. This paper describes the rationale for and design of the 3D longitudinal Study which aims to: (i) describe diet quality changes in the 12 months following T2D diagnosis, (ii) identify the demographic, physical and psychosocial predictors of sustained improvements in diet quality and glycemic control, and (iii) identify associations between glycemic control and diet quality in the 12 months following diagnosis. This cohort study will recruit adults registered with the Australian National Diabetes Services Scheme who have been recently diagnosed with T2D. Participants will be involved in five purposefully developed telephone surveys, conducted at 3 monthly intervals over a 12-month period. Diet quality will be determined using a 24-h dietary recall at each data collection point and the data will be scored using the Dietary Approaches to Stop Hypertension (DASH) diet-quality tool. This study is the first dedicated to observing how people newly diagnosed with T2D change their diet quality over time and the predictors of sustained improvements in diet and glycemic control.

## 1. Introduction

Diet quality plays a vital role in helping people with type 2 diabetes (T2D) to achieve and maintain optimal glycemic control, thereby lowering their risk of developing diabetes-related complications [1]. Diet quality can be described as the extent to which food intake complies with national or international dietary guidelines or a priori diet quality score [2]. Investigating diet quality based on dietary patterns, defined as multiple dietary components operationalized as a single exposure [3], provides valuable information, beyond analyzing specific nutrients (e.g., protein) or food groups (e.g., dairy) [4]. This is because dietary patterns closely reflect actual dietary behavior and have a stronger influence on disease risk than specific nutrients or foods [5]. Findings from dietary pattern analyses may facilitate the translation of useful recommendations to health professionals and the general population [5,6]. A dietary pattern rich in whole-grains, fruits, vegetables, legumes, and nuts; moderate in alcohol; and low in refined grains, red or processed meats, and sugar-sweetened beverages has been shown to improve glycemic control in people with T2D [7]. Consequently, a key feature of international T2D management recommendations is to eat healthy foods that provide a high-quality diet [8,9,10].

However, evidence has shown that people with T2D have low-quality diets, despite these recommendations [10,11,12,13,14,15]. Our recent systematic review identified that internationally, people with T2D do not adhere to food group recommendations outlined in dietary guidelines [15]. Qualitative studies examining lived experiences report that people with T2D find it challenging to adopt and maintain healthy dietary behaviors after diagnosis [13,14]. Our previous qualitative study that investigated the experiences and perceptions of Australian adults newly diagnosed with T2D found that while participants reported making immediate, widespread changes to dietary behaviors that led to improvements in diet quality initially, they found it challenging to maintain dietary change [13]. Participants described feeling restricted in food choice, being uncertain of ideal dietary behaviors and felt unheard and rushed when speaking about their diet with health professionals [13]. Similar results were obtained in a qualitative study in Mexico where people reported making only short-term adherence to improvements in dietary intake due to difficulties with controlling appetite and eating with others [14]. While these qualitative findings of experiences raise concerns, it is important to also investigate quantitative aspects of diet quality change following diagnosis. 

Cross-sectional research has assessed the diet quality of people with T2D at a single-point in time [15], however, no research has quantitatively explored changes in diet quality after diagnosis. Consequently, there is no evidence as to whether diet quality remains fixed once an individual is diagnosed with T2D, or whether there are periods of marked increases or decreases in diet quality. Prospective, observational studies are valuable as they measure events in temporal sequence and can distinguish causes from effects [16,17]. Many factors influence diet quality. These include non-modifiable factors such as age and sex, and modifiable factors such as self-efficacy, perception of current diet, environmental factors such as marketing and food availability, and relationships with health professionals [11,13]. There is currently no data on the demographic and health characteristics influencing diet quality change for people with T2D [13,18]. There is a clear need to investigate how diet changes over time so targeted strategies can be developed to facilitate improved glycemic control. 

This paper describes the methodological protocol of the 3D Longitudinal Study, so named because seeing something in three dimensions adds clarity. In this case it refers to the 3D’s of Diet, after Diagnosis with Diabetes. The study aims are to: (i)Describe diet quality changes in the 12 months following T2D diagnosis. (ii)Identify the demographic, physical and psychosocial predictors of improvements in diet quality and glycemic control. (iii)Identify associations between glycemic control and diet quality in the 12 months following diagnosis.

## 2. Theoretical Framework

The ability to predict and explain health-related behavior is important for developing strategies to change those behaviors [19]. The theory of planned behavior (TPB) is among the most influential and widely applied theories of the factors influencing health-related behavior [19]. According to the TPB, the single best predictor of a person’s behavior is the intention to perform that behavior [20]. This is predicted by three constructs: attitude, subjective norm, and perceived behavioral control (PBC). The greater the PBC and more favorable the attitude and subjective norms, the stronger the intent will be to perform the behavior [20]. According to the TPB, people with T2D will intend to improve their diet quality to the extent that they believe the likely outcomes of consumption to be favorable, perceive social pressure from those who are important to them and feel capable of improving their diet quality without difficulty [21]. The constructs of the TPB are considered strong predictors of healthful eating and are commonly applied in the development of dietary behavior change interventions [21,22]. This study will integrate the TPB into its design in order to explore the factors that may serve as moderators in influencing the TPB constructs, thus affecting dietary behaviors and T2D management. 

## 3. Materials and Methods 

### 3.1. Study Design 

The 3D Longitudinal Study is a prospective observational cohort study that will be conducted in Australia between 2018–2019. The study will recruit people newly diagnosed with T2D and monitor their dietary intake over 12 months. The Strengthening the Reporting of Observational Studies in Epidemiology (STROBE) checklist for cohort studies was used to guide the development of the research protocol [23]. The 3D Longitudinal Study is registered with the Australian New Zealand Clinical Trials Registry (ANZCTR) (ref: ACTRN12618000375257) and was approved by the Griffith University Human Research Ethics Committee (ref: 2017/951). Study results will be published in peer-reviewed journals and presented at scientific conferences. 

### 3.2. Potential Participants 

Eligible participants will be adults aged 18 years or older who have been recently diagnosed with T2D (<6 months prior to recruitment contact), are registered with the Australian National Diabetes Service Scheme (NDSS) and have indicated their willingness to be contacted for research purposes. The NDSS is an initiative of the Australian Government and is administered with the assistance of Diabetes Australia [24]. In 2017, there were approximately 1.1 million people registered with the NDSS [25]. Registration is part of usual care for people diagnosed with T2D, therefore this potential participant pool provides broad representation of the target population. People with T2D are authorized to register for free if they live in Australia or are visiting from a country with which Australia has a Reciprocal Health Care Agreement on an applicable visa [24]. Registering with the NDSS enables individuals to access a range of government approved diabetes-related products and information services [24]. All registrants have the option of consenting to being contacted for research purposes. Upon registration, patients are required to register their personal details on a form signed by a registered Australian medical practitioner, nurse practitioner or a credentialed diabetes educator [24]. The majority of T2D diagnoses in Australia are made by general practitioners (GPs), who are the usual coordinators of management [7]. A detailed participant inclusion and exclusion criteria is listed in Table 1.

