### 3.3. Participant Recruitment and Screening

A convenience sample of all individuals registered with the NDSS with a new diagnosis of T2D over the previous 6-month period will be sent an initial invitation letter and a plain-language summary of the research project via email by Diabetes Australia. Interested individuals will be invited to contact the research team via email or telephone to confirm eligibility, provide informed consent and arrange data collection. Participants will be informed they can withdraw from the study at any stage. This recruitment method has been trialed in a feasibility study conducted in 2016–2017 (unpublished) which successfully recruited 22 participants from 1000 email invitees. Of these 22, 17 completed baseline data collection, six participants had left the study by 3 months, however all participants remaining at 3 months were retained to 12 months.

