### 3.4. Data Collection

Data will be collected using a purpose-developed, interviewer-administered telephone surveys at five-time points; baseline, and then at 3, 6, 9, and 12 months after commencing the study. Surveys will be conducted by Accredited Practicing Dietitians (APDs). The feasibility study found each survey takes approximately 30 min to complete. A measuring tape will be posted to all participants within two working days of recruitment to provide enough time to measure their waist circumference before data collection begins. Strategies including contact and scheduling methods have been shown to improve cohort retention in longitudinal studies [26]. Participants will be contacted 2 weeks prior to their next anticipated data collection round to schedule a time. All participants will be sent a reminder via their preferred contact method (email or text message) one day prior to the date of their next survey. The recruitment and contact process is outlined in Figure 1.

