## Figures and Tables

**Figure 1 nutrients-11-00158-f001:**
[figure not shown]
Recruitment and contact process for the 3D Longitudinal Study.

**Table 1 nutrients-11-00158-t001:** Inclusion and exclusion criteria for the 3D Longitudinal Study.

Inclusion Criteria	Exclusion Criteria
Adults aged >18 years	Individuals aged <18 years.
Diagnosed with T2D <6 months prior to recruitment contact	Diagnosed with LADA, T1D, gestational diabetes or pre-diabetes
Registered with the Australian NDSS and indicated their willingness to be contacted for research purposes.	Individuals who have been placed on a special diet due to a co-morbidity (e.g., renal disease)
Able to communicate in English	

LADA, Latent Autoimmune Diabetes in Adults; NDSS, National Diabetes Service Scheme; T1D, Type 1 diabetes; T2D, Type 2 diabetes.

**Table 2 nutrients-11-00158-t002:** Overview of data collection points in the 3D Longitudinal Study.

Data Collection Methods	Time Collected				
	0 Months	3 months	6 Months	9 Months	12 Months
Diet quality	✔	✔	✔	✔	✔
Glycemic control	✔	✔	✔	✔	✔
Medication use	✔	✔	✔	✔	✔
Baseline demographic factors	✔				
Physical factors	✔	✔	✔	✔	✔
Psychosocial factors	✔	✔	✔	✔	✔
Exposure to allied healthcare support	✔	✔	✔	✔	✔

**Table 3 nutrients-11-00158-t003:** Dietary Approaches to Stop Hypertension (DASH) dietary pattern scoring criteria.

Component	Foods	Scoring Quintiles (Q) *
Fruits	All fruits and fruit juices	Q1 = 1 point Q2 = 2 points Q3 = 3 points Q4 = 4 points Q5 = 5 points
Vegetables	All vegetables except potatoes and legumes	
Nuts and legumes	Nuts and peanut butter, dried beans, peas, tofu	
Whole-grains	Brown rice, dark breads, cooked cereal, whole-grain cereal, other grains, popcorn, wheat germ, bran	
Low-fat dairy	Skim milk, yogurt, cottage cheese	
Sodium	Sum of sodium content of all foods	Q1 = 5 points Q2 = 4 points Q3 = 3 points Q4 = 2 points Q5 = 1 point
Red and processed meats	Beef, pork, lamb, deli meats, organ meats, hot dogs, bacon	
Added sugar	Foods and beverages with added sugars (i.e., sugar sweetened beverages)	

* Q1 represents low consumption and Q5 represents high consumption.

**Table 4 nutrients-11-00158-t004:** Healthful Eating Beliefs Scale rationale for investigation and modes of responses.

Category	Rationale for Investigation	Area of Enquiry	Standardized Questions and Response Options	Source

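### The aims and the model text count time from diagnosis, but entry runs to almost 6 months after diagnosis and visits are timed from enrolment, so the observed year only partly matches the target year

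*Protocol article*

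**What the plan says.** **Target.** Section 1 of the protocol article gives aim (i) as "Describe diet quality changes in the 12 months following T2D diagnosis" and aim (iii) as "Identify associations between glycemic control and diet quality in the 12 months following diagnosis". Aim (ii) carries no such window. Section 3.8 says the model will weigh diet change directly after diagnosis against change in the medium term, for a 12-month outcome.

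**Entry.** Section 3.2 admits people "recently diagnosed with T2D (<6 months prior to recruitment contact", and Table 1 repeats the limit: "Diagnosed with T2D <6 months prior to recruitment contact". Section 3.3 matches this, since people "with a new diagnosis of T2D over the previous 6-month period will be sent an initial invitation letter". The steps to baseline come after the invitation: "Interested individuals will be invited to contact the research team via email or telephone to confirm eligibility, provide informed consent and arrange data collection". The article states no maximum time for them.

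**Clock.** Section 3.4 places the surveys at "baseline, and then at 3, 6, 9, and 12 months after commencing the study".

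**Use.** Section 3.6.1 labels participants improvers or maintainers from the change in DASH score between baseline and 3 months. Section 3.8 uses interim change, mainly at 3 months, as an explanatory variable. Section 3.6.2 retrieves HbA1c results over the 12-month study period.

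**Expected timing.** Section 1 reports from the authors' own qualitative study that "participants reported making immediate, widespread changes to dietary behaviors". The same sentence adds that the changes were hard to maintain.

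**The concern.** Two time origins are used as if they were one. The aims and the interpretation of the model start at diagnosis, while the visits and the improver split start at enrolment. The gap between the two can approach half of the 12-month target window and twice the 3-month interval used to classify participants.

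If the plan is followed as written, a change seen between months 6 and 9 after diagnosis will be reported as early change for one participant and pooled with months 0–3 for another. A visit near month 18 will be reported as the 12-month outcome. Aim (iii) has the same mismatch, because HbA1c is also collected on the study clock.

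The early period matters most here, because the authors' own earlier work places dietary change there. Someone who improved at once and held steady before a late baseline would be classed as a maintainer. So would someone who improved and was already relapsing, since section 3.6.1 puts a fall of 3 points or more in the same group. The improver label could then carry information about when a person was recruited as well as about what that person did.

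**Working it through.** The plan gives no figure to reproduce, so the check is timeline arithmetic.

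**Inputs**
- Target window: months 0 to 12 after diagnosis (section 1, aims i and iii).
- Time from diagnosis to recruitment contact, g: 0 to just under 6 months (sections 3.2 and 3.3, Table 1).
- Lag from contact to baseline survey, L: not stated. Assumed to be 0, 0.5 or 1 month.
- Visits at 0, 3, 6, 9 and 12 months on the study clock (section 3.4).

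**Formulas**, with d = g + L, the months from diagnosis to baseline:
- Observed window = [d, d + 12].
- Overlap with the target window = 12 − d months, or (12 − d)/12 as a share.
- Baseline-to-3-month change covers [d, d + 3].
- Last visit at d + 12.

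**Results** (g = 6 stands for the upper limit)

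| g | L | Baseline-to-3-month change covers | Last visit | Overlap | Visits within 12 months of diagnosis |
|---|---|---|---|---|---|
| 0 | 0 | months 0–3 | 12 | 12/12 = 100% | 5 of 5 |
| 3 | 0 | months 3–6 | 15 | 9/12 = 75% | 4 of 5 |
| 6 | 0 | months 6–9 | 18 | 6/12 = 50% | 3 of 5 |
| 6 | 0.5 | months 6.5–9.5 | 18.5 | 5.5/12 = 46% | 2 of 5 |
| 6 | 1 | months 7–10 | 19 | 5/12 = 42% | 2 of 5 |

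**Average, under an assumption.** If g is uniform on 0 to 6 months and L = 0, the mean of d is 3. The mean overlap is then 12 − 3 = 9 months (9/12 = 75%), the last visit falls at month 15 on average, and half the cohort has its baseline 3 months or more after diagnosis. The article does not give the distribution of entry times, so this is an illustration.

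**Spread at one label.** Two participants at the same nominal visit can differ by about 6 months in time since diagnosis, and 6/3 = 2 times the classification interval.

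**The case against.** The entry window is stated openly in three places, and section 3.1 describes the design accurately as recruiting newly diagnosed people and following them for 12 months. No collected data become invalid, and change from enrolment can still be estimated. This stands, and it limits the problem to what is claimed and to how time enters the analysis.

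A reader might infer that the study does not observe the year after diagnosis at all. The arithmetic does not support that, because the overlap is partial and is complete for anyone enrolled at diagnosis.

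A reader might also infer that early improvement is underestimated, that late entrants tend to be labelled maintainers, or that a given percentage of the change is missed. Such a percentage needs an assumed entry distribution and an assumed speed of change towards a stable new level, and the article gives neither. The qualitative result it cites has no timing in weeks or months. It also describes improvement followed by difficulty in maintaining it, so a late baseline could be near the peak, past it or back at the starting level. The direction is open.

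Finally, one might say that diagnosis timing is not collected. That does not follow, because eligibility depends on it, so it has to be ascertained for each person. Section 3.8 names its explanatory variables by group, and a condensed article may leave a covariate to the full plan. The point does not need that omission, since the stated aims, entry window and visit clock already conflict.

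**Conclusion.** The point holds as an inconsistency between stated parts of the plan. From the documents alone, the baseline-to-3-month change covers anything from months 0–3 to about months 6–9 after diagnosis, and the 12-month visit falls about 12–18 months after it. The observed window overlaps the target year by about 50–100%. A scheduling lag of 0.5 to 1 month (assumed) lowers the bottom of that range to 46–42%. The 75% average rests on uniform entry.

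The effect on results is a plausible risk only. Some early change may precede baseline, and the improver label may partly reflect time since diagnosis, but neither size nor direction can be derived. The limitations in section 4 do not mention the issue.

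**What to change.** 1. Carry the date of diagnosis, already needed to confirm eligibility, into the analysis dataset.
2. In the longitudinal model, use months since diagnosis as the time axis or include it as a covariate. Include it also in the analyses of improver status. On a diagnosis-based axis, the earliest months are informed only by people who enrolled early.
3. Reword aims (i) and (iii), and the phrase in section 3.8 that places the early change directly after diagnosis, to *the 12 months after enrolment in people diagnosed within the previous 6 months*.
4. State in the limitations that change before baseline is not observed. No model can recover it for the individual participant, so steps 3 and 4 are needed even if step 2 is done.

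A subgroup enrolled soon after diagnosis is optional and should be labelled exploratory. The documents give no cut-off for it, and it would be small. Taking 6 to 8 weeks as an example, uniform entry over about 26 weeks gives 6/26 = 23% to 8/26 = 31% of entrants. At the feasibility yield of 17 completed baselines per 1000 invited (section 3.3), that is 17 × 0.23 ≈ 4 to 17 × 0.31 ≈ 5 people per 1000 invitations.

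The cost is a narrower claim and slightly more analysis work. The main changes need no extra participants or visits.

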### 3.3. Participant Recruitment and Screening

A convenience sample of all individuals registered with the NDSS with a new diagnosis of T2D over the previous 6-month period will be sent an initial invitation letter and a plain-language summary of the research project via email by Diabetes Australia. Interested individuals will be invited to contact the research team via email or telephone to confirm eligibility, provide informed consent and arrange data collection. Participants will be informed they can withdraw from the study at any stage. This recruitment method has been trialed in a feasibility study conducted in 2016–2017 (unpublished) which successfully recruited 22 participants from 1000 email invitees. Of these 22, 17 completed baseline data collection, six participants had left the study by 3 months, however all participants remaining at 3 months were retained to 12 months.

### 3.4. Data Collection

Data will be collected using a purpose-developed, interviewer-administered telephone surveys at five-time points; baseline, and then at 3, 6, 9, and 12 months after commencing the study. Surveys will be conducted by Accredited Practicing Dietitians (APDs). The feasibility study found each survey takes approximately 30 min to complete. A measuring tape will be posted to all participants within two working days of recruitment to provide enough time to measure their waist circumference before data collection begins. Strategies including contact and scheduling methods have been shown to improve cohort retention in longitudinal studies [26]. Participants will be contacted 2 weeks prior to their next anticipated data collection round to schedule a time. All participants will be sent a reminder via their preferred contact method (email or text message) one day prior to the date of their next survey. The recruitment and contact process is outlined in Figure 1.

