Change in DASH score from baseline to 3 months will be used to categorize participants as diet quality improvers or diet quality maintainers. Participants will be split into 2 groups; those who improved their DASH score by at least 3 DASH points (Diet quality improvers) and those who maintained their DASH score within 2.99 points or decreased their DASH score by at least 3 points (Diet quality maintainers). A change in DASH score of 3 points was selected based on findings from previous literature [40]. In a 20-year longitudinal study of over 40,000 adults, an average DASH score of 23.8 out of 40 was observed, and a change in score of approximately 3 points or more was sufficient to significantly influence long-term glycemic control [40]. 

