Dietary intake data will be obtained through the Australian version of the Automated Self-Administered 24-h Dietary Assessment Tool (ASA-24). The ASA-24 is based on the validated Automated Multiple-Pass Method (AMPM) which is considered the optimal method for obtaining 24-h recall data due to its numerous probes, standardization of interviewer administration and validation against recovery biomarkers [41,42]. This method is also consistent with the methodology of the most recent population nutrition survey in Australia (the National Nutrition Survey) and has been shown to be a valid measure of dietary behavior at a given time point [43,44]. The ASA-24 is an online automated questionnaire that guides the individual through a system designed to maximize respondents’ opportunities for remembering and reporting foods eaten in the previous 24 h [45]. The questionnaire is divided into five phases in line with published methodological guidelines; ‘quick list’, ‘forgotten foods’, ‘time and occasion’, ‘detail cycle’, and ‘final probe’ [45]. These phases encourage respondents to think about their intake in different ways and from several perspectives which has been shown to reduce bias in the estimation of dietary intake [45]. Once a specific food or beverage is reported, systematic questions are asked to capture more precise information about the food, cooking methods and quantity consumed. The ASA-24, usually a self-completed tool, will be adapted for use in a telephone survey; a researcher will ask the questions and enter the data. This will reduce participant burden and help decrease any bias associated with participant information technology literacy levels. This process was carried out successfully in a feasibility study with patients newly diagnosed with T2D. The data from the feasibility study was able to be used to assess changes in diet quality over a 12-month period. 

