Following data collection, participant 24-h dietary recall data will be sent from the ASA-24 program to the research team. This data will then be manually entered into FoodWorks by an experienced dietitian to allow determination of participant DASH scores. FoodWorks is a dietary analysis software program using standardized serve sizes that allows for quantification of specific food groups (e.g., vegetables) and nutrients (e.g., sodium) obtained from reported dietary intakes, recipes and meals [46]. FoodWorks draws on the national AUSNUT database [47]. AUSNUT was developed by Food Standards Australia and New Zealand and includes complete nutrient data sets of Australian foods designed specifically for nutrition surveys and is therefore suitable for use in this project [47]. 

DASH scores will be calculated using the standard scoring tool created by Fung et al [39]. Every tenth DASH score will be cross-checked by a second member of the research team to ensure accuracy. The standard scoring tool determines a score between 8 and 40 points, with 40 points representing optimal accordance with the DASH dietary pattern [39]. The DASH score is calculated by summing the number of daily servings of seven dietary components; fruits, vegetables, nuts and legumes, whole-grains, low-fat dairy, red and processed meats, added sugar, and sodium intake. For each of the components, participants are classified according to their intake ranking. Higher intakes of fruits, vegetables, low-fat dairy, whole-grains, and nuts and legumes receive higher scores. For example, quintile 1 is assigned 1 point and quintile 5 is assigned 5 points. Intake of sodium, red and processed meats and added sugars are scored in reverse as these are less desirable foods [39]. The lowest quintile is given a score of 5 points and the highest quintile is given a score of 1 point. The components scores are then summed to give an overall DASH score [39]. The scoring criteria for the DASH-style diet is outlined in Table 3.

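### Each DASH score rests on one recalled day, and neither the scheduling nor the listed model variables account for weekday versus weekend: a small, cheaply removable error

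*Protocol article*

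**What the plan says.** The Abstract sets one recall per wave: "Diet quality will be determined using a 24-h dietary recall at each data collection point". Section 3.6.1 describes the instrument as built to "maximize respondents’ opportunities for remembering and reporting foods eaten in the previous 24 h", so each score reflects a single day. There are five waves: "baseline, and then at 3, 6, 9, and 12 months after commencing the study".

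On booking, section 3.4 says "Participants will be contacted 2 weeks prior to their next anticipated data collection round to schedule a time", followed by a reminder one day before the call. It gives no day-of-week rule. For the first call, section 3.3 has interested people contact the team, who then arrange data collection.

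The scores are used in two ways:

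- Section 3.6.1: "Change in DASH score from baseline to 3 months will be used to categorize participants as diet quality improvers or diet quality maintainers". Improvers are "those who improved their DASH score by at least 3 DASH points (Diet quality improvers"; all others are maintainers.
- Section 3.8 takes DASH at 12 months as the primary outcome. Its explanatory variables are glycemic control, interim diet change (mainly at 3 months), medication, demographic, physical and psychosocial measures, and healthcare support. The type of day recalled is not among them.

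The Discussion acknowledges measurement error in dietary assessment in general terms, without mentioning day of the week or number of recall days.

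**The concern.** What people eat may differ between weekdays and weekends. With one recalled day per wave, a participant who recalls a Saturday at baseline and a Tuesday at 3 months has a change score made up of true change, ordinary day-to-day variation and the weekend difference. The cut is close enough for this to matter to an individual: "The standard scoring tool determines a score between 8 and 40 points", and since "quintile 1 is assigned 1 point and quintile 5 is assigned 5 points", a one-quintile shift in three of the eight components moves the total by 3 points.

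Three things could be affected:

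- **The individual label.** The improver or maintainer label can change with the days that happened to be recalled.
- **Mean change (aim i).** This is biased if the share of weekend recalls differs between waves.
- **Predictors (aim ii).** If household circumstances affect when someone can take a call of about 30 minutes, day type may be related to a predictor such as income or living arrangement. Part of that predictor's apparent effect on 12-month DASH would then belong to the day of the call.

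Unlike ordinary day-to-day variation, this component can be identified from the recall date and removed without collecting more data.

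**Working it through.** The article states no SD, weekend effect, sample size or power, so there is no figure of its own to reproduce. The check asks how much day type could matter over a range of assumptions.

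**Inputs from the article:** one recall per wave (Abstract); improver cut of at least 3 points from baseline to 3 months, on a scale of 8 to 40 in one-point steps (3.6.1).

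**Assumed inputs:** DASH lower by d = 1 to 2 points on weekend days; single-day SD 4 to 5; correlation between two single-day scores (ICC) 0.2 to 0.5; no true change; recalled days spread evenly over the week.

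**1. SD of change** = SD × √(2(1 − ICC)).
- Smallest: 4 × √(2 × 0.5) = 4.0.
- Largest: 5 × √(2 × 0.8) = 6.3.

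**2. Chance of a false improver label.** Scores are whole numbers, so P = P(Z > (2.5 − shift)/SD of change). The shift is 0 for same-type days, +d for weekend to weekday and −d for weekday to weekend.

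| Baseline to 3 months | Change SD 4.0 | Change SD 6.3 |
|---|---|---|
| Same day type | 26.6% | 34.6% |
| Weekend to weekday, d = 1 | 35.4% | 40.6% |
| Weekend to weekday, d = 2 | 45.0% | 46.9% |
| Weekday to weekend, d = 1 | 19.1% | 29.0% |
| Weekday to weekend, d = 2 | 13.0% | 23.8% |

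The ranges are therefore about 27-35%, 35-47% and 13-29%.

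**3. How often the two days differ in type.** With a weekend share of 2/7: 2 × (2/7) × (5/7) = 0.41, or 0.204 in each direction. With a weekend share of 1/5: 2 × 0.2 × 0.8 = 0.32.

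**4. Net effect on the overall false-improver share** at d = 2, with 0.592 of pairs on same-type days:
- Change SD 4.0: 0.592 × 26.6% + 0.204 × (45.0% + 13.0%) = 27.6%, against 26.6% if matched.
- Change SD 6.3: 0.592 × 34.6% + 0.204 × (46.9% + 23.8%) = 34.9%, against 34.6% if matched.

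The rise is about 0.3 to 1 percentage point.

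**5. Share of variance.** Day type adds 0.41 × d² to the change variance: about 1.6 at d = 2 and 0.41 at d = 1. Against a change variance of 16 to 40, that is 4-10% at d = 2 and 1-3% at d = 1.

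**6. Sensitivity.** Take a within-person SD of 2 to 5 directly, the cut at exactly 3 and d = 2. The false-improver share goes from 14.4% to 16.7% at SD 2, 24.0% to 24.9% at SD 3, 29.8% to 30.3% at SD 4, and 33.6% to 33.8% at SD 5. The net effect passes 1 point only when one-day variation is small.

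**7. When bias arises.** The bias in a mean is the difference in weekend share times d. If two predictor groups differed by 40 percentage points in weekend share and d were 2 (both assumed), their 12-month DASH contrast would be off by 0.4 × 2 = 0.8 points, or 0.8/3 = 27% of the 3-point cut. The same arithmetic gives the bias in mean change when the weekend share differs between two waves. A larger sample does not reduce either.

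**The case against.** **The article is condensed.** Call slots and the use of the recall date may be set in the full protocol, the interviewer manual or the analysis plan. The contact-process figure cited in section 3.4 is not shown, and section 3.8 lists broad classes of variables rather than a closed set. This stands as a limit: one can say that the scheduling and variables described take no account of day type, not that the study has no rule. If a rule exists, one sentence settles the point.

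**The net effect is small.** Most false improver labels come from ordinary variation between single days, which day-type control leaves untouched. This stands, and it sets the severity.

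**A stable link between a predictor and call day cancels in a change score.** That is right for change, if the link is the same at both waves. It does not answer section 3.8, where the outcome is the 12-month score itself.

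**Stronger readings the article does not support.** A reader might infer that calls are booked at whatever time suits the participant, but section 3.4 says only that a time is scheduled. A reader might also infer that Friday and Saturday intake is never sampled; that needs Monday-to-Friday calling, which is not stated. Nor does anything show that the day mix actually differs between waves. Baseline and follow-up calls are arranged differently, which leaves room for a difference but does not demonstrate one.

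**Conclusion.** The point holds as a minor one. The article fixes one recalled day per wave and a 3-point cut on the difference of two such days, while the scheduling and explanatory variables it describes ignore day type. With a weekend effect of 1 to 2 points and a change SD of 4.0 to 6.3, all assumed, day type can shift an individual's chance of a false improver label appreciably in either direction. It raises the overall false share by no more than about 1 percentage point (up to 2.3 points if the within-person SD is as low as 2).

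It would be wrong to conclude that day type accounts for most misclassification or invalidates the improver grouping: 27-35% of unchanged participants would be labelled improvers even with matched days. Bias in mean change or in predictor effects is conditional on a day mix that differs between waves or is related to predictors of 12-month DASH. The article neither shows this nor describes a safeguard against it.

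**What to change.** - **Analysis (3.8).** Derive recalled-day type, weekday or weekend, from the recall date. Include it as a covariate in every DASH model, both for 12-month DASH and for change from baseline to 3 months.
- **Scheduling (3.4).** Book calls so that the weekday/weekend mix of recalled days is similar at each wave, and match a participant's baseline and 3-month day type where feasible.
- **Avoid fixing one day type per person for all five waves.** That would tie day type to the participant in the 12-month outcome, leave the covariate almost no within-person variation, and mean that some participants' weekend diet is never measured.

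The cost is a sentence in each section, slightly less scheduling flexibility, and some evening or weekend calls. No extra recalls are needed. The change does not reduce ordinary one-day variation, which is a separate matter.
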